### Safety Analysis

The descriptive method will be used for the safety evaluation, and safety variables include adverse event, dose interruption for adverse event, vital signs, laboratory measurement (complete blood cell count, routine urinalysis and serum chemistry), standard 12-lead ECG and physical examination findings.

Type, severity, frequency and the relationship with the investigational product will be tabulated for description for all the adverse events occurred during the study. The subjects that occurred the adverse events leading to withdraw from study and serious adverse events will be particularly noted. Adverse events will be coded using the Medical Dictionary for Regulatory Activities (MedDRA). The shift table will be used for the lab test. Abnormal test items with clinical significance need to be listed.

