## Exclusion criteria

1. Subjects who are allergic or known to be allergic to venlafaxine and desvenlafaxine
2. Subjects who have previously failed treatment with venlafaxine at an adequate dose for an adequate time, or patients who have refractory depression and have previously failed treatment with at least 2 types of antidepressants at an adequate dose for an adequate time;
3. Subjects who have greater than 25% change in HAM-D17 total score at baseline from screening visit;
4. Subjects who have clear suicide attempt or behavior with Suicide score in HAM-D17 ≥ 3 points;
5. Pregnant or breastfeeding women, or men and women of childbearing age who do not use a medically acceptable form of contraception or fail to continue contraception until 28 days after the last dose of the study medication;
6. Subjects with DSM-IV-TR axis I diagnoses other than MDD, who receive treatment for such diagnoses (including current or previous diagnoses of anorexia nervosa or bulimia nervosa), or who have been diagnosed with depressive neurosis within the past 2 years; Depressive episode secondary to other psychiatric disorder or somatic disease;
7. Subjects with MDD secondary to other organic or mental disorders;
8. Subjects with a history of seizures (except spasms caused by infantile hyperpyretic convulsions);
9. Subjects who have received electroconvulsive therapy (ECT) within 3 months prior to screening or need current ECT treatment per investigator’s judgment, have received systematic psychotherapy (interpersonal relationship therapy, dynamic therapy, cognitive behavioral therapy) within 3 months of screening, have received transcranial magnetic stimulation (TMS) 3 months prior to screening, or have received light therapy 2 weeks prior to screening;
10. Subjects who have regularly taken anti-depressants within 2 weeks prior to screening, or have withdrawn from psychotropic drugs for less than 7 half-lives (at least 2 weeks for monoamine oxidase inhibitors and at least 1 month for fluoxetine) before randomization/enrollment;
11. Subjects with a history of serious unstable cardiovascular, hepatic, renal, blood or endocrine diseases;
12. Subjects with hypertension whose blood pressure is poorly controlled (SBP≥140 mmHg or DBP≥90 mmHg at the screening and baseline visit);

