## Safety Indicators

- Adverse event
- Vital signs, physical examination, laboratory tests (hematology, urinalysis, blood chemistry test and serological test), 12-lead ECG findings

Patients will be followed up by investigators according to the scheduled procedure, vital signs, laboratory examinations and adverse events will be checked and recorded. Unexplainable laboratory outliers should be re-measured immediately, until they are recovered to normal and/or can be well explained.

All the adverse events occurred during the study should be recorded in CRF. Evaluation of adverse event includes classification, grade, relationship with the drug, therapeutic measures and outcome.

For the subjects prematurely withdrawn, every effort should be made to determine the reason for the withdrawal, record the time of withdrawal from the study precisely and complete all the examinations at the last visit.

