### Risks and precautions during the study

1. Excerbation of clinical symptoms and suicide

For patients at any age with major depressive disorder, their disease may be possibly exacerbated, regardless of the administration of antidepressants, and they are likely to have suicidal ideation and suicidal behavior as well as abnormal change of behavior, and this risk may continue until the condition is significantly relieve. Depression is known to be associated with some mental disorders and suicide risk, and these mental disorders themselves are the strongest signs of suicide.

For all the subjects receiving the study drug (Ansofaxine Hydrochloride Extended Release Tablet or placebo) for treatment, exacerbation of their clinical symptoms, suicidal tendency and abnormal change in behavior should be closely observed, in particular in the initial stage of drug treatment.

When antidepressants are used for treatment of adult and pediatric patients with major depressive disorder, other psychotic or non-psychotic disorders, the following symptoms may appear: anxiety, agitation, panic attack, insomnia, irritability, hostility, aggression, impulsiveness, restlessness (psychomotor restlessness), hypomania and mania. Although the correlation of the occurrence of the above symptoms with exacerbation of depression and/or suicidal impulse has not been identified, these symptoms may be the foreboding of suicide.

For the subjects with persistent exacerbation of depressive symptoms, suicide or signs associated with it, discontinuation of study drug should be considered, in particular for those whose symptoms are severe, occur suddenly or newly appear.

In this study, the subjects with suicide risk should be excluded.

1. Prolonged QT interval

The in vitro study showed that Ansofaxine Hydrochloride could inhibit the potassium channel coded by hERG, however, no prolonged QT interval was seen overall in the animal study, nor clinically significant prolongation of QT interval was seen in the phase I clinical trial on tolerability. In order to ensure subject’s safety, subjects with clinically significant abnormality on ECG (in particular prolonged QTc interval) should be excluded, and will be monitored through ECG during the study.

1. Blood Pressure

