## AE record(s)

The adverse event record form should be filled in truthfully during the study. Its correlation with the study drug will be evaluated based on comprehensive consideration of complications and concomitant medications, through detailed record of its type, intensity, time of occurrence, duration, therapeutic measure and treatment.

All the physical examination and laboratory examination findings required in the study protocol should be recorded in the subject’s CRF. The physical examination and laboratory examination findings after administration will be compared with that prior to administration, the change must be evaluated as to judge if it meets the definition of adverse event if it is indicative of exacerbation of clinical status, and all the changes determined to meet the definition of adverse event will be recorded in Section Adverse event in CRF.

The medical document on adverse event should be recorded in the original document, including the laboratory examination report form.

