Appendix 1: Hamilton Depression Scale -17 (HAM-D_17_)

| *Note: 5-grade scoring method with 0～4 points is used for most items. Criteria on each grade: (0) none; (1) mild; (2) moderate; (3) severe; (4) very severe. 3-grade scoring method with 0～2 points is used for few items, the grading criteria are: (0) none; (1) mild to moderate; (2) severe* | | | |
| --- | --- | --- | --- |
| **Item** | | | **Score** |
| 1 | Depressed mood (sad, hopeless, helpless, worthless) | 0=no symptom; 1=narrate only when asked;  2= express spontaneously in conversation;  3= nonverbal expression of this emotion (e.g., through expression, posture, voice and desire to cry);  4= complete expression of this emotion almost by self speech and nonverbal expression | \|_\| |
| 2 | Feeling of guilt | 0=no symptom; 1= blame yourself and feel that you have failed others;  2= Think that you have committed a crime, or think about previous mistakes or misconducts repeatedly;  3= Think of your current illness as a punishment for your own mistakes, or have evil delusion;  4= Hear accusations or condemnations and/or have threatening illusion | \|_\| |
| 3 | Suicide | 0=no symptom; 1=feel pointless in living;  2= Wish I have died or think of something related to death frequently;  3= Negative thought (suicidal thought) or suicide posture  4= Suicidal attempt (any serious attempt will be scored 4) | \|_\| |
| 4 | Trouble falling asleep | 0 = No difficulty in falling asleep;  1= Have a chief complaint of difficulty in falling asleep sometimes (e.g., still unable to fall asleep 30min after going to bed);  2= Have a chief complaint of difficulty in falling asleep every night | \|_\| |
| 5 | Shallow sleeping | 0 = No symptom;  1= Have a chief complaint of shallow sleep at midnight, frequent nightmare;  2 = Wake up at midnight (before 12:00pm) – any case of waking up will be scored 2 (not including  going to the toilet) | \|_\| |
| 6 | Early awakening | 0 = No symptom;  1= Have early awakening, but be able to fall asleep again;  2= Fail to fall asleep again after early awakening | \|_\| |

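### Suicidality is the first risk the protocol names, and HAM-D17 item 3 is rated at every visit, but the safety variables omit the item, so worsening ideation not reported as an adverse event appears in no planned safety analysis

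*Protocol*

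**What the plan says.** **The named risk.** Section 8.2, under Risks and precautions during the study, lists three risks. The first is exacerbation and suicide. Of patients with major depressive disorder it says that "they are likely to have suicidal ideation and suicidal behavior as well as abnormal change of behavior", and for everyone on study drug or placebo it asks that "exacerbation of their clinical symptoms, suicidal tendency and abnormal change in behavior should be closely observed, in particular in the initial stage of drug treatment". The other two are QT prolongation and blood pressure.

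**The measurement.** The study flow chart schedules HAM-D17 at screening, at baseline, at Weeks 1 and 2, at Week 4, and at Week 6 or termination. Appendix 1 grades item 3 (Suicide) from 0 to 4. The second-highest grade reads "3= Negative thought (suicidal thought) or suicide posture" and the highest is an attempt. Exclusion criterion 4 already draws on the item at entry: "Subjects who have clear suicide attempt or behavior with Suicide score in HAM-D17 ≥ 3 points".

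**The safety variables.** Section 8.2 gives adverse events and then "Vital signs, physical examination, laboratory tests (hematology, urinalysis, blood chemistry test and serological test), 12-lead ECG findings". The Abstract repeats that list. Section 11.2, Safety Analysis, states that "safety variables include adverse event, dose interruption for adverse event, vital signs, laboratory measurement" and goes on to ECG and physical examination. No HAM-D17 item is among them.

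**The route to an adverse event.** Section 9.1 describes one comparison with pre-dose values: "The physical examination and laboratory examination findings after administration will be compared with that prior to administration". Rating-scale items are not mentioned there.

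**The concern.** Two of the three named risks are matched to a safety variable and the first is not, although a graded measure of it is taken at every visit. Item 3 enters the planned analyses only as one seventeenth of the HAM-D17 total, or inside a factor score, and both are efficacy outputs. As written, emergent ideation becomes visible as safety information only if an investigator also records it as an adverse event.

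The trial's primary objective is to find the optimal dose, so how a named risk varies across 40, 80, 120 and 160 mg/day and placebo is part of what it should report. The protocol stresses the first weeks of treatment, and item 3 is rated at Weeks 1 and 2, which is when a systematic rating would be most useful.

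**Working it through.** The protocol gives no figure on this point to reproduce. The check sets the risks against the variables and then does arithmetic on the scale.

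**1. Risks against safety variables**

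| Risk named in 8.2 | Matching variable in 8.2 and 11.2 |
| --- | --- |
| Exacerbation and suicide | none beyond adverse events in general |
| QT prolongation | 12-lead ECG |
| Blood pressure | vital signs |

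**2. Weight of item 3 in the total.** Appendix 1 has 9 items scored 0–4 (items 1, 2, 3, 7, 8, 9, 10, 11, 15) and 8 scored 0–2 (items 4, 5, 6, 12, 13, 14, 16, 17; the code 3 on item 16 means not evaluated).

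- Maximum total = 9 × 4 + 8 × 2 = 36 + 16 = 52.
- Share of item 3 = 4 / 52 = 7.7% at most.

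**3. Effect of worsening on the arm mean.** Shift in mean total = proportion affected × rise on item 3. The proportions are assumptions.

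| Proportion of an arm of 52 | Subjects | Rise on item 3 | Shift in arm mean |
| --- | --- | --- | --- |
| 5% | 2.6 | 2 points | 0.1 |
| 10% | 5.2 | 2 points | 0.2 |

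Shifts of this size cannot be recognised in a mean on a 52-point scale.

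**4. Response and remission.** Take a subject who enters at the minimum total of 20 with item 3 = 0. At Week 6 item 3 is 3 and the other items sum to 4.

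- Final total = 3 + 4 = 7.
- Reduction = (20 − 7) / 20 = 65%.

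This subject is a responder (at least 50% reduction) and a remitter (total at most 7) with a new rating at the suicidal-thought grade. The pattern is extreme, but it shows that these endpoints do not screen for item-3 worsening.

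**5. Factor scores.** The secondary variable is change in HAM-D17 factor scores at the end of treatment. The protocol does not say which factor holds item 3. A mean factor score, even if summarised by visit, does not count individuals who worsened.

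**6. Missing items.** Section 11.2 allows a total to be derived when up to 20% of items are missing: 0.20 × 17 = 3.4, so 3 items. A total can therefore exist for a visit at which item 3 was not rated.

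**7. What a table with 52 per arm can show.** P(at least one subject) = 1 − (1 − p)^52 for an assumed true rate p.

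| Assumed p | P(at least one of 52) |
| --- | --- |
| 1% | 41% |
| 2% | 65% |
| 5% | 93% |
| 10% | 99.6% |

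If none of 52 is observed, the one-sided 95% upper limit is 1 − 0.05^(1/52) = 5.6%. The table can describe the data but cannot settle small differences between doses.

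**The case against.** The strongest reply is that a table of one scale item is ordinary content for a statistical analysis plan, that the protocol says such a plan will follow, and that the verb in "safety variables include adverse event, dose interruption for adverse event, vital signs, laboratory measurement" does not close the list. This stands in part. The layout of the table can wait for that plan. The choice of safety variables, however, is something this protocol does fix: it lists them in three places, and its Abstract goes as far as naming shift tables for laboratory tests, ECG and physical examination. At that level of detail, leaving out the measure for the first-named risk is a weakness of this document.

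The second reply is that other routes exist, and this stands in full for reported events. Any unfavourable medical event from consent to the last visit is to be recorded, with its type, intensity, time of occurrence and duration. Subjects are asked about adverse events at each treatment visit. All adverse events are coded and tabulated, and serious events and withdrawals due to adverse events are specially noted. Suicide during the study is a withdrawal criterion. A reader might therefore infer that suicidality is wholly hidden in the efficacy score, or that its timing is lost. The documents do not support that. Section 9.1 says how examination and laboratory findings are screened; it does not confine adverse events to them.

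Three further readings also go too far.

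- **That the item-3 ratings have no safety use.** Section 8.2 requires close observation for suicidal tendency, and nothing stops a rater from acting on the item. What is absent is a planned safety analysis.
- **That any net gain with a worse item 3 counts as success.** A 10-point gain on other items with a 2-point rise on item 3 is a net 8 points. From an entry total of at least 20 that is at most 40%, so it is not response; the total stays at 12 or more, so it is not remission.
- **That exclusion criterion 4 is a simple score threshold.** It joins an attempt or behaviour with the score, so some subjects might enter with item 3 at 3. A shift from baseline allows for this; a bare count of high scores would not.

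**Conclusion.** The point holds in a limited form. Suicidality is the first risk named, item 3 is rated at all six visits, and none of the listed safety variables uses it, while QT and blood pressure each have a matching variable. What would be missed is new or worsened ideation that is scored on item 3 and not reported as an adverse event. Reported events are covered.

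How often ideation would be scored but not reported cannot be derived from the protocol. The calculations show only that the efficacy analyses would not reveal it: at most 7.7% of the scale range, and about 0.1 to 0.2 points on an arm mean if 5% to 10% of the arm rose by 2 points. Those proportions are assumptions.

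A reader might infer that formal comparisons of each dose with placebo are needed. The protocol's safety method is descriptive, and with 52 per arm a zero count excludes only rates above 5.6%, so a descriptive display is the right level. This is a worthwhile improvement to safety reporting. It does not affect the primary analysis.

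**What to change.** Add HAM-D17 item 3 to the safety variables in 8.2 and in the Safety Analysis part of 11.2, and to the matching row of the Abstract. Specify one descriptive output on the safety set, by treatment arm:

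- a shift table of baseline against worst post-baseline item-3 score;
- the number and percentage, by visit, with any increase from baseline;
- the number and percentage, by visit, with a new score of 3 or more (baseline below 3).

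Use observed item scores only, include the termination visit, and do not carry values forward or fill in item 3 from other items. Show the number with the item rated as the denominator at each visit, and count missing ratings in their own row. No hypothesis tests are needed.

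The cost is a short text change and one more safety table from data already collected. Sample size, alpha, visits, scales, staff and clinical management rules stay as they are.

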### Interim Analysis

No interim analysis is planned in this study.

### Data monitoring committee

This study will not use a Data Monitoring Committee.

# Quality control and assurance

1. This clinical study will be carried out in CFDA certified drug clinical trial institutions. The study personnel have the professional knowledge and experience required for this clinical study and are relatively stable.
2. Prior to the start of the study, all the investigators participating in this study will be organized to study the protocol carefully, as to be familiar with the study methods and procedures, and implement each technical indicator.
3. Prior to the start of the study, relevant scale assessor will be trained on the consistency of scale evaluation.
4. Subject’s cooperation is very important. They will be asked to understand the significance of this study fully, cooperate with treatment and observation actively as required in the study protocol.
5. Other drugs and therapies affecting judgment of results are contraindicated during the study.
6. The laboratory has established standard operating procedure and quality control procedure for laboratory observational variables.
7. The sponsor and study unit will establish quality control and quality assurance systems, respectively.
8. The sponsor will appoint monitors, as to make sure the subject’s rights are guaranteed during the study, the study record and reported data are authentic, accurate and complete without error, and the study complies with the approved protocol, GCP and relevant regulations.
9. During the study, monitors will monitor the progress and quality of the study on a regular basis, as to ensure the study is carried out according to the protocol, and verify CRF, as to ensure consistency with the original data.
10. The study drug will be maintained by the person in charge of drug management, locked in a specially assigned counter and kept at room temperature. The residual drugs will be stored separately and registered for the amount, and returned to the sponsor centrally at the end of the study.
11. Archive keeping, data processing and correction of relevant testing instrument need to be managed by specially assigned person.

# Ethical requirements

## Good Clinical Practice

This clinical study will be carried out in accordance with the Declaration of Helsinki and GCP requirement. The study protocol will be conducted only upon approval by the ethics committee. Investigators will make sure that this clinical study is conducted in accordance with the laws, regulations, scientific and ethical standards of the People's Republic of China on medical research.

## Informed consent

Subjects need to sign a written informed consent form prior to enrollment in the study (screening or any other activity related with the study). Investigators will explain the materials related with the study drug to each subject sufficiently, including the property, objective, procedure, observational variables, examinations, possible risks and benefits, as well as possible adverse reactions subject’s rights and duties, and provide sufficient time for subjects to consider the content related with the study, as to make the decision on whether to participate in it. Subject’s personal information will be strictly confidential, unless required by laws, subject’s identity, privacy and test results will not be revealed.

## Early termination of the trial

If the frequency and severity of adverse event imply potential risk of the study drug to human health, this clinical study will be terminated. The sponsor, ethics committee and relevant regulatory authorities should be reported prior to the termination.

# Summary Report

Enrollment and observation of all the cases are expected to be completed in 12 months in this clinical study. Upon completion of observation of all the cases, biostatisticians will carry out statistical analysis of all the data and issue the statistical analysis report, provide to the leading unit of this study to issue summary report.

# Amendment to study protocol

In case amendment to the study protocol is found during the study, it needs to be discussed by the principal investigator and the sponsor jointly, and approved through signature of both parties. After amendment to the protocol, it can be carried out only upon putting on file/approval by the ethics committee. If any important new material involving the investigational product is found, the informed consent form needs to be modified in a written form and submitted to the ethics committee for review, and subject’s consent must be obtained again.

# Publication

Investigators can publish or disclose the results of the clinical study after end of the clinical study, however, a prior writtern approval from the sponsor is needed. For multi-center clinical study, the principal investigator must make sure that the data at one single study site can not be published or disclosed in advance prior to publication or disclosure of the complete study results.

The sponsor or its representative will reserve the right to review the first draft before publication or disclosure of the study results. This is not to restrict or prevent investigators from publishing or disclosing clinical study results, but to protect intellectual property information owned by the sponsor or its representative, and allow the sponsor or its representative to provide advice on the clinical study results planned to be published or disclosed based on the information not yet available to investigators.

